**Study projects**:

## The effect of behavioral activation play therapy in adolescents with depression: a study protocol for a randomized controlled trial

Principal Investigator and Organizer:

[name]

Department of Child and Adolescent Psychiatry

The Affiliated Brain Hospital of Guangzhou Medical University

Guangzhou 510100, China

[contact]

Email: [contact]

Status: Mar. 17, 2022

**The effect of behavioral activation play therapy in adolescents with depression: a study protocol for a randomized controlled trial**

Study Group

This project is a collaboration between the Guangzhou Medical University and the Department of Child and Adolescent Psychiatry, the Affiliated Brain Hospital of Guangzhou Medical University.

Principal Investigator

[name], Department of Child and Adolescent Psychiatry of the Affiliated Brain Hospital of Guangzhou Medical University, Guangzhou 510100, China. E-mail: [[contact]](mailto:[contact]), [contact]

Major scientists involved in the Probiotics Study

[name], the Affiliated Brain Hospital of Guangzhou Medical University, Guangzhou, China

[name], the Affiliated Brain Hospital of Guangzhou Medical University, Guangzhou, China

[name], the Affiliated Brain Hospital of Guangzhou Medical University, Guangzhou, China

[name], the Affiliated Brain Hospital of Guangzhou Medical University, Guangzhou, China

[name], the Affiliated Brain Hospital of Guangzhou Medical University, Guangzhou, China

[name], the Southern Medical University, Guangzhou, China

[name], Guangzhou Medical University, Guangzhou, China

Synopsis

In this study, we integrated behavioral activation (BA) and gamified physical activities (GPA) to create behavioral activation play therapy (BAPT). This is the first RCT to explore the effectiveness and adaptability of BAPT in adolescents with depression. This study will provide evidence that may help to decrease depressive symptoms in adolescents, and will demonstrate the treatment effectiveness in terms of increasing levels of physical activity, reducing the rate of non-suicidal self-injury behaviors, and improving sleep quality. We also hope to assess other possible clinical effects of BAPT.

Participants aged 12 to 17 years will be eligible if they are defined as having depression by using DSM-5, but if they meet one of the following exclusion criteria they will not be allowed to take part: (1) Participants with a DSM-5 diagnosis of other mental disorders, including addictive disorders, developmental disorders, bipolar disorder, substance-related disorders, and schizophrenia (except anxiety disorders); (2) Participants with severely disruptive or aggressive behaviors, or positive suicidal ideation (suicide item scores of the MADRS > 4); (3) Participants with severe psychotic symptoms (presence of pain or common hallucinations and/or delusions); (4) Participants with clinically significant and uncontrolled pulmonary, endocrine, immunological, cardiovascular diseases (based on ancillary examination, physical examination, medical history); (5) According to the research group, participants who could not cooperate with the cognitive function tests or would not be suitable for this study.

Prior to participation in this study, all subjects and their legal guardians must be fully informed about the project and sign a written informed consent form. The participants will be divided into intervention group and control group according to a pre-defined randomization protocol. The intervention and control groups received 4 weeks of BAPT and 4 weeks of BA respectively. Participants in both groups will be treated and cared for according to the same criteria, but will not be involved in any other psychological therapy programs.

Therapeutic effect evaluation will be done at the baseline, week 2 (the end of the basic intervention), week 4 (the end of all the high-order intervention), week 8, and week 16 by the MADRS, BDI-II-C, BADS-SF, ANSAQ, ISI, IPAQ-SF, and Likert Scale. The primary outcome was whether BAPT could decrease depressive symptoms in adolescents by MADRS scores.

# Background

## Epidemiology

From 2012 to 2022, the incidence of depression in adolescents increased dramatically[1]. In 2020, 17.2% and 7.4% of adolescents in China were found to have mild and severe depressive symptoms, respectively, and the lifetime prevalence is expected to be 11%–20%[2]. The high prevalence of depression in adolescents is a public health issue because it can interrupt the developmental process and have negative effects throughout life[3, 4]. Adolescent major depressive disorder (MDD) can have serious consequences such as dropping out of school, drug use, self-harm, and suicide, and it is the main cause of illness and disability among adolescents. Currently, clinical guidelines recommend psychotherapy and medication for adolescents with depression[5]. However, psychotherapy is associated with a number of drawbacks, as it can often be difficult to access, costly, and minimally effective. Furthermore, some medications prescribed to treat adolescent MDD, such as fluoxetine and venlafaxine, have unfortunate side effects including increasing suicidal thoughts and behaviors in adolescents. As a result of these drawbacks, some adolescents with depression do not benefit from medication and psychotherapies[6]. Accordingly, effective interventions are an important focus for mental health researchers around the world[7, 8].

## Physical activity

In recent years, exercise therapy has attracted worldwide attention because of its simplicity and strong effects[9]. For instance, the effects of high and moderate intensity exercise have been shown to be comparable to those of antidepressant treatment[10]. Consequently, clinicians have adopted an increasingly positive attitude towards the use of exercise in treating adolescents with MDD[11]. In 2020, the World Health Organization (WHO) recommended that children and adolescents engage in at least one hour of moderate-to-high physical activity (PA) every day to improve health and reduce symptoms of depression[12]. However, research showed that only 20% of children and adolescents aged 13–15 comply with this recommendation[13]. Adolescents with depression are even less likely to engage in exercise, as depressive symptoms reduce the motivation to exercise[14]. Therefore, more effective treatment strategies are urgently needed.

## Behavioral activation

In 2023, the WHO recommended behavioral activation (BA) as an effective form of psychotherapy for the treatment of depression and suggested that antidepressants should not be used as first-line treatment for adolescents[15]. BA is clinically as effective as cognitive behavioral therapy (CBT), costs up to 21% less[16], and is simple and easy to administer. Although BA is an effective treatment for adolescents with depression, it is difficult to conduct in the adolescent population and outcomes have been found to be insufficient[17]. As a result, health practitioners have attempted to apply BA in combination with other therapeutic techniques to obtain better treatment results in adolescents with depression[18-20]. For example, the combination of BA with digital networking technology was well received by adolescents[21, 22], but this program led to an increase in screen time. Besides, increased screen time in adolescents may lead to a decrease in social and physical activity as well as an increase in sedentary behavior[23]. Furthermore, the depression risk increases in individuals who exceed two hours of screen time per day[24].

## BA combined with PA

BA including PA can improve mood, which is beneficial for patients with depression, along with increasing the amount of regular exercise[16]. Studies have shown that BA interventions combined with PA have a high completion rate, and that they can significantly reduce depressive symptoms in patients. BA and PA are highly consistent in terms of techniques and methods, such as self-monitoring, goal setting, and problem-solving techniques. Combining them could overcome the limitations of using each intervention alone, as well as reduce the recurrence rate of depression after treatment[25].

Although studies have demonstrated that BA combined with PA is feasible and acceptable for improving depressive symptoms in adults, fewer studies have been conducted in adolescents. This may be because different age groups choose different forms of PA. In contrast to traditional forms of PA, adolescents are more inclined to select game forms of PA[26]. Therefore, it is crucial to increase the degree to which physical activities are perceived as pleasurable when developing therapies for use in this population[27]. Studies have shown that using gamification to promote physical activity can lead to better uptake[28], indicating that interventions that focus on gamified physical activity (GPA) may be a practical way to reduce sedentary behavior and depression risk in adolescents[29]. In most adolescents, play is a vital element of PA interventions, and the integration of play-centered activities is likely to be an effective method for increasing the level of PA and improving social connections. Indeed, encouraging adolescents to participate in active, stimulating, and adventurous play could enable them to test their abilities independently, thus improving social resilience[30-32]. Using competition and rewards may help to promote physical activity, along with other more innovative approaches[33].

## Study objectives

To date, no empirical studies have verified the effects of interventions that integrate GPA into BA with the goal of improving depressive symptoms in adolescents with depression in clinical settings in China. As a result, there are no guidelines regarding the parameters of exercise necessary for anti-depressive effects. To address this, our research group integrated BA and GPA into behavioral activation play therapy (BAPT), and developed a randomized controlled trial (RCT) to evaluate the efficacy of BAPT for treating adolescents with depression. We plan to assess the effectiveness of BAPT in increasing levels of physical activity, reducing non-suicidal self-injury behavior, and ameliorating sleep quality. We also hope to discern the adaptability of this treatment in terms of clinical applications.

## Hypotheses

Primary: BAPT (intervention group) will be more effective than BA (control group) in relieving depressive symptoms and enhancing treatment adherence in adolescents with depression.

Secondary: BAPT (intervention group) will be more effective than BA (control group) in increasing levels of physical activity, reducing non-suicidal self-injury behavior, and ameliorating sleep quality.

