
At the baseline, week 2 (the end of the basic intervention), week 4 (the end of all the high-order intervention), week 8, and week 16, participants from the two groups will be evaluated with the corresponding scales to assess the degree of depression, behavioral activation level, non-suicidal self-injury behavior, and sleep quality scores. We will also calculate the improvement of symptoms for each dimension in each group at each time point, and then compare the divergences between the two groups. All participants will receive an electronic exercise wristband as a reward after they completed the follow-up.

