## Data analysis

The study is based on the intention-to-treat principle. SPSS 28.0 will be used for data analysis. First, to ensure comparability after randomization, we will compare the differences between the groups at the baseline. The continuous variables will be analyzed by a t-test when the data have a normal distribution, and non-normally distributed data will be analyzed using the Mann-Whitney U test. Baseline differences between groups in terms of sociodemographic and clinical variables will be assessed using Chi-square tests for categorical variables and an analysis of variance (ANOVA) for continuous data. To compare intervention effects, a mixed-effect regression model will be used. Group (BAPT or BA) will be used as an inter-subject factor, and time (baseline, post-treatment, and follow-up) as an intra-subject factor. We will utilize Cohen's d to achieve both the intra- and intergroup analyses. P < 0.05 was set as statistically significant.

Financial Support

This study was supported by Science and Technology Program of Guangzhou (grant No. 205171098044), Guangzhou Municipal Key Discipline in Medicine (2021-2023), Guangzhou High-level Clinical Key Specialty, and Guangzhou Research-oriented Hospital.

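### Three secondary superiority claims, compared visit by visit at a flat P < 0.05 with no deciding measure or visit, carry more than the nominal error rate

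*Protocol*

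**What the plan says.** Four parts of the protocol bear on this point.

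- **Hypotheses.** The section reads: "Secondary: BAPT (intervention group) will be more effective than BA (control group) in increasing levels of physical activity, reducing non-suicidal self-injury behavior, and ameliorating sleep". These are three separate domains, each stated as superiority in one direction.
- **Synopsis.** The study "will demonstrate the treatment effectiveness in terms of increasing levels of physical activity, reducing the rate of non-suicidal self-injury behaviors, and improving sleep quality".
- **Efficacy evaluations.** After baseline, assessments fall at "week 2 (the end of the basic intervention), week 4 (the end of all the high-order intervention), week 8, and week 16". Improvement is to be calculated "for each dimension in each group at each time point, and then compare the divergences between the two groups". The list of constructs just before that sentence names depression, behavioral activation, self-injury and sleep, but not physical activity. Physical activity reaches the same visits through the Synopsis, which schedules assessment at baseline, weeks 2 and 4, and "week 8, and week 16 by the MADRS, BDI-II-C, BADS-SF, ANSAQ, ISI, IPAQ-SF, and Likert Scale".
- **Data analysis.** Intervention effects are compared with a mixed-effect regression model. It has group as a factor and a time factor of three levels: baseline, post-treatment and follow-up. The decision rule is "P < 0.05 was set as statistically significant".

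Physical activity has two sources of data. IPAQ-SF is in the list of secondary outcome measures. Wristband intensity is collected weekly (Physical activity intensity; Fig. 2 footnote). The protocol does not say which one answers the hypothesis.

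**The concern.** The protocol settles three things together: which secondary claims it hopes to make, that the arms are compared at every visit, and that 0.05 is the threshold throughout. It does not say which measure, visit or model contrast decides each claim. The model's three time levels do not settle this either. There are five assessments, and follow-up could mean week 8, week 16 or both.

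Followed as written, one nominally significant result on one scale at one visit could be reported as showing that BAPT reduces self-injury, improves sleep or raises activity. The claim would look like a 5% test but would be the best of several. The self-injury and sleep claims matter most, because they could influence how the therapy is used in adolescents.

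The point concerns the secondary hypothesis only. It does not touch the MADRS primary outcome or the sample size.

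**Working it through.** **Plan's own figure.** The protocol states no familywise error rate, so there is none to reproduce.

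**Inputs from the protocol**
- Domains: 3 (Hypotheses). Instruments: IPAQ-SF, ANSAQ, ISI (Synopsis; Efficacy evaluations).
- Post-baseline visits: 4, at weeks 2, 4, 8 and 16.
- Threshold: 0.05 per test (Data analysis). It is taken as two-sided because the sample size section uses a two-sided 0.05.

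**Inputs assumed**
- No true difference on any of the three domains at any visit.
- Correlations between domains and between visits, for which the protocol gives no values.

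**Step 1: independent tests.** The chance of at least one significant result among m tests is 1 − (1 − α)^m. For results favouring BAPT only, α is 0.025.
- 3 domains × 4 visits, m = 12: 1 − 0.95^12 = 46.0%; favouring BAPT, 1 − 0.975^12 = 26.2%.
- One test per domain, m = 3: 1 − 0.95^3 = 14.3%; favouring BAPT, 1 − 0.975^3 = 7.3%.

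**Step 2: correlated tests.** Test statistics were simulated under the null (400,000 draws, multivariate normal). The correlation was the product of an exchangeable domain part and an exchangeable visit part. A result counts as significant if |z| > 1.96, and as favouring BAPT if z > 1.96 in that direction.

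| Tests | Correlation between domains | Correlation between visits | Any significant, two-sided | Favouring BAPT |
| --- | --- | --- | --- | --- |
| 3 × 4 | 0 | 0 | 46% | 26% |
| 3 × 4 | 0 | 0.5 | 40% | 22% |
| 3 × 4 | 0.5 | 0.5 | 36% | 18% |
| 3 × 4 | 0.5 | 0.7 | 30% | 15% |
| 3 × 4 | 0.8 | 0.8 | 21% | 11% |
| 3 × 1 | 0 | – | 14.3% | 7.3% |
| 3 × 1 | 0.5 | – | 12.6% | 6.3% |
| 3 × 1 | 0.8 | – | 9.8% | 4.9% |

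**Step 3: comparison with nominal.** The two-sided rate is 5%, of which 2.5% lies in the direction of BAPT.
- Visit by visit, favouring BAPT: 11 / 2.5 to 26 / 2.5, about 4 to 10 times nominal.
- One test per domain, favouring BAPT: 4.9 / 2.5 to 7.3 / 2.5, about 2 to 3 times nominal.

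**Step 4: if physical activity is left out of the visit-by-visit comparison**, as the list in Efficacy evaluations would allow, m = 8. Independent tests then give 1 − 0.95^8 = 33.7%, and 1 − 0.975^8 = 18.3% favouring BAPT. These are the values without correlation; positive correlation lowers them.

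**Step 5: after the fix.** With one test per domain, Holm's first step uses 0.05 / 3 = 0.0167. Under the global null with independent tests, the chance of any rejection is 1 − (1 − 0.0167)^3 = 4.9%.

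**The case against.** The strongest objection is that multiplicity among secondary outcomes is usually settled in the statistical analysis plan, which is not shown. That stands as far as it goes: the missing adjustment alone would not be a finding. What remains is what the protocol does fix, namely three claims of superiority, a comparison at each time point and one flat threshold. An analysis plan would have to narrow those statements, not just fill a gap.

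Second, Data analysis names a mixed model, which can be read as giving one test per outcome. The sentence on time points mentions neither a test nor a p-value. This reading is fair, and its smaller figures are shown. It still leaves two to three times the nominal rate, and it does not say which contrast decides.

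Third, physical activity is absent from the list in Efficacy evaluations, so the count of 12 relies on the Synopsis. This also stands; Step 4 shows the effect. Likewise, IPAQ-SF is the activity measure listed as a secondary outcome, which favours it over the wristband, but the hypothesis names neither.

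Fourth, the protocol calls these outcomes secondary, sizes the trial on depression scores alone, and elsewhere in the Synopsis speaks of exploring effectiveness. A reader might infer from the Hypotheses and the promise to demonstrate that the three domains are formal confirmatory endpoints. The text is mixed and does not go that far.

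**Conclusion.** The point holds in a limited form. The protocol's wording allows a false secondary claim for BAPT at a rate above the nominal 2.5%: about 5-7% with one test per domain, and about 11-26% with three domains compared at four visits. Counting differences in either direction, the figures are about 10-14% and 21-46%, against 5%. All assume that no domain truly differs, and the ranges reflect correlations chosen for illustration.

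Two stronger readings are tempting and not supported. A reader might infer about a 30-36% chance of a false secondary claim. That band needs particular correlations that the protocol does not give, takes the 12-test reading as certain, and counts results favouring BA, which cannot support a hypothesis that BAPT is better. A reader might also infer that the secondaries must be tested only after a significant MADRS result. Nothing in the protocol requires this; it is a design choice that an analysis plan may settle.

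**What to change.** In Hypotheses and Data analysis, name for each of the three domains one measure and one deciding visit, or one mixed-model contrast. For physical activity, say whether IPAQ-SF or the wristband decides. Apply Holm at two-sided 0.05 across the three tests. Report all other secondary measures and visits as estimates with 95% confidence intervals, without significance claims. Gating the three tests on the MADRS result is optional.

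The alternative is to label all secondaries exploratory and, in the Synopsis, change *will demonstrate* to *will explore*.

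Either route changes wording only and needs no extra participants or assessments. The price of the first is some power: the smallest of the three p-values must be below 0.0167 before any of the three can be claimed.

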# Methods and design

## Study design and setting

This study is a two-arm single-blind RCT. The intervention and control groups will receive 9 sessions of BAPT and 9 sessions of BA, respectively. Because adolescents with depression who are hospitalized generally have a relatively short stay in the hospital, the participants in this study will complete the first 4 sessions during hospitalization and then will be asked to return to the department for the remaining 5 sessions after they are discharged.

This study was approved by the ethics committee of the Affiliated Brain Hospital of Guangzhou Medical University on April 27, 2023 (Ethics number: 2023 [027]) and registered with the China Clinical Trials Center under the registration number ChiCTR2300072671. The design of this protocol is in line with the Standard Protocol Items: Recommendations for Intervention Trials (SPIRIT). **Fig. 1** presents the enrolment, intervention and evaluation schedule for SPIRIT. **Fig. 2** presents a flow chart of the study. The study will be supervised by the Department of Child and Adolescent Psychiatry (DCAP) and the Academic Management Committee of the Affiliated Brain Hospital of Guangzhou Medical University.

### Fig. 1 Study period

[figure not shown]

**Abbreviations:** ***BMI***: Body Mass Index; ***MADRS***: Montomery-Asberg Depression Rating Scale; ***BDI-Ⅱ-C***: Beck Depression Inventory-China; ***BADS-SF***: Behavioral Activation for Depression Scale Short Form; ***ANSAQ***: Adolescent Non-suicidal Self-injury Assessment Questionnaire; ***ISI***: Insomnia Severity Index; ***IPAQ-SF***: International Physical Activity Scale Short Form; ***Physical activity intensity***: collecting data regarding calorie consumption (kcal) and metabolic equivalents; ***Likert Scale***: assessing the acceptance of the intervention by patients and their families.

### Fig. 2 Research flow chart

[figure not shown]

*****Participant data regarding physical intensity were collected every week during the study.

## Recruitment

Participants will be recruited at the Department of Child and Adolescent Psychiatry in the Affiliated Brain Hospital of Guangzhou Medical University. Prior to screening, researchers will offer an explanation of the study process to the participants and their legal guardians, along with the significance of the study, risks, and benefits. All participants and their legal guardians will to partake the study voluntarily, as indicated by signing an informed consent form, and will be able to withdraw at any time in the process of the study. The interventions provided in the study will be free of charge.

## Participant selection

Participants were diagnosed with depression based on the DSM-5 by two senior experts in the same field. Listed in **Table 1** are the inclusion and exclusion criteria for adolescents with depression.

